##### Mapping of brain development atlas

Based on the preprocessed MRI and EEG data, we use FreeSurfer to quantify the volumes of brain regions such as the hippocampus and prefrontal cortex, and calculate the normal range of brain region volumes related to age. Calculate and plot the curves of the volumes of specific brain regions of children by gender through non-linear functions as they change with age, and identify the critical windows of development for specific brain regions in infants. Extract time-frequency features such as α/β wave power from EEG data, construct a functional connectivity matrix, and analyze the development pattern of the resting-state EEG network through graph theory analysis and independent component analysis. Use canonical correlation analysis to explore the coordinated development relationship between the volume of MRI brain regions and the functional connectivity of EEG. At the same time, conduct piecewise regression on longitudinal data, detect the mutation points of the brain development rate, and verify its correlation with the development scores in terms of intelligence, cognition, and behavior, so as to comprehensively depict the dynamic development trajectory of brain structure and function.

##### Construction of infant brain development models

Integrate the volumes of MRI brain regions, time-frequency features of EEG, inflammatory indicators during pregnancy, and questionnaire scores of children in different ability areas. Reduce the dimensionality through principal component analysis to generate multimodal feature vectors and input them into a Transformer to construct a deep learning model. Train the model using cross-validation and prevent overfitting through the Dropout method and the AdamW optimizer. Take the AUC as the core index, and simultaneously calculate the sensitivity, specificity, accuracy, and other indicators of the model. Verify the generalization ability of the model using an international public database, and locate the key predictive factors through the SHapley Additive exPlanations (SHAP) values and the Local Interpretable Model-agnostic Explanations (LIME) algorithm. Combine the anatomical localization of brain regions to explain the risk prediction mechanism of how inflammation during pregnancy affects brain development, and ensure the clinical application value of the model.

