#### Follow-up plan

Utilizing an aggregation cross design, referencing the grouping methodology of the Baby Connectome Project (BCP) by UNC/UMN in the USA (12), participants were categorized into 9 sub-cohorts based on the age at initial enrollment, each having varying sampling density and age spans (Table 1). Each of the first three sub-cohorts enrolled 536 participants, while sub-cohorts 4–9 each enrolled 268 participants, totaling 3,216 participants. Each participant was followed up 3–4 times, yielding data from 11,256 participant—visits. Moreover, the follow-up intervals for sub-cohorts 1–3 and 4–9 were 3 and 6 months, respectively, ensuring sufficient sampling density during the first year, which is critical for rapid development in language and socio-emotional skills. Oversampling was strategically implemented during milestones of language and socio-emotional development and periods prone to scan failures (before the age of 3). Considering the low cooperation levels of infants and potential dropouts, 3,847 participants were recruited to ensure the acquisition of high-quality data from 3,216 subjects (Figure 1).

**Table 1 T1:** Cohort design and follow-up time planning schedule.

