##### Risk model construction

Using deep-learning-based artificial intelligence technology, we will develop an early risk assessment model for the impact of maternal inflammation on infant brain development. This model will be able to integrate data on maternal inflammation during pregnancy to predict the brain development of children with high precision and further identify potential risks in infant intelligence, motor skills, emotions, and cognition. Through rigorous training and validation, our goal is to ensure that the area under the curve (AUC) of the model's recognition ability for relevant developmental disorders reaches 0.8 or above.

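### SHAP/LIME attribution in a model that holds inflammation together with the brain measures cannot show how inflammation affects brain development

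*Protocol article*

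**What the plan says.** In the protocol article, Risk model construction (under Primary outcome) states: "we will develop an early risk assessment model for the impact of maternal inflammation on infant brain development". Its numerical target is that the "area under the curve (AUC) of the model's recognition ability for relevant developmental disorders reaches 0.8 or above".

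Under Data analysis, Construction of infant brain development models sets out the steps:
- Inputs: "Integrate the volumes of MRI brain regions, time-frequency features of EEG, inflammatory indicators during pregnancy, and questionnaire scores of children in different ability areas".
- Reduction: "Reduce the dimensionality through principal component analysis to generate multimodal feature vectors and input them into a Transformer". It is not stated whether the PCA is run jointly or within each modality, or how much variance is kept.
- Attribution: "locate the key predictive factors through the SHapley Additive exPlanations (SHAP) values and the Local Interpretable Model-agnostic Explanations (LIME) algorithm".
- Interpretation: "Combine the anatomical localization of brain regions to explain the risk prediction mechanism of how inflammation during pregnancy affects brain development".

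The section on family environment and parenting patterns, also under Data analysis, plans secondary correlations of CRP and IL-6 with brain volume, cortical thickness and EEG power, and comparisons of children grouped by inflammatory level. It names mediation analysis for parenting patterns only.

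**The concern.** The interpretive step makes a statement about cause and pathway: how an exposure changes the brain. Its only inputs are attributions from a predictor that contains the exposure and, beside it, the brain measures through which the exposure may act. No step in that section models inflammation as a cause of the brain measures, or compares a path through the brain with one outside it.

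Attributions answer a different question, namely how much the fitted prediction moves with each input given the others. A region important for predicting delay will be flagged in children of healthy mothers too. The risk is that a list of good predictors is reported, under a primary outcome, as the mechanism of maternal inflammation, or that a low score for inflammation is taken as evidence against an effect.

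**Working it through.** The article gives no figure on this point, so there is nothing to reproduce. Path strengths, noise levels and feature counts below are assumptions.

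**1. Exact linear case.** Let I be inflammation (SD 1), M the true brain mediator (SD 1) with correlation a with I, and Y = bM + error. The brain measure is W = M + noise, with reliability λ and noise variance v = (1−λ)/λ. The model regresses Y on I and W. Then:
- coefficient of I = a·b·v/(1−a²+v)
- coefficient of W = b(1−a²)/(1−a²+v), multiplied by SD(W) = √(1+v) to put it on the SHAP scale
- in a linear model with normal inputs, mean |SHAP| is proportional to |coefficient| × SD, which gives the shares

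| λ | a | I (units of b) | W (units of b) | Share of I |
|---|---|---|---|---|
| 1 | 0, 0.3, 0.6 | 0 | 1.000 | 0% |
| 0.7 | 0 | 0 | 0.837 | 0% |
| 0.7 | 0.3 | 0.096 | 0.813 | 10.6% |
| 0.7 | 0.6 | 0.241 | 0.716 | 25.2% |
| 0.5 | 0.3 | 0.157 | 0.674 | 18.9% |
| 0.5 | 0.6 | 0.366 | 0.552 | 39.9% |

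Example, λ = 0.7 and a = 0.3: v = 0.3/0.7 = 0.4286; I = 0.3 × 0.4286/(0.91 + 0.4286) = 0.096; W = 0.91/1.3386 × √1.4286 = 0.813; share = 0.096/(0.096 + 0.813) = 10.6%.

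Three consequences follow:
- **The region.** At λ = 0.7 its attribution is 0.837b when inflammation leaves it untouched and 0.813b when a = 0.3. Being flagged says nothing about whether inflammation altered it.
- **Confounding.** If a shared cause produces the correlation a and inflammation does nothing, the joint distribution of I, W and Y is the same, so the share is again 10.6%.
- **Direct action.** With no path through the brain and a direct effect of 0.096b, the share is 0.096/(0.096 + 0.837) = 10.3%.

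**2. Many-feature simulation.** A ridge-logistic predictor stood in for the Transformer, with linear SHAP carried back to the raw features. There were 5 inflammation, 30 brain (8 affected), 10 EEG and 5 questionnaire features, n = 3,216 as planned, 60 runs per cell, and PCA keeping 80% of variance. Test AUC was 0.81 to 0.83, near the article's target.

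| Share of total SHAP | No effect | Mediated, a = 0.3 | Mediated, a = 0.6 | Direct only, 0.3 |
|---|---|---|---|---|
| Inflammation, raw features | 5.9% | 7.2% | 7.5% | 9.4% |
| Inflammation, PCA within modality | 4.9% | 5.0% | 6.3% | 9.1% |
| Inflammation, joint PCA | 1.4% | 8.9% | 16.7% | 9.8% |
| 8 affected regions, raw features | 57.6% | 55.3% | 52.4% | 55.6% |
| 8 affected regions, PCA within modality | 45.9% | 59.7% | 54.9% | 44.8% |
| 8 affected regions, joint PCA | 29.1% | 27.0% | 27.8% | 26.7% |

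Under joint PCA the inflammation share separates mediation (a = 0.3 or 0.6) from no effect, but not mediated from direct action (8.9% against 9.8%). Within modality, the inflammation share hardly moves at a = 0.3, while the regional share does.

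**3. Sensitivity to data structure.** Other joint-PCA simulations at n = 3,216 gave inflammation shares, for a = 0, 0.3 and 0.6, of 1.3%, 1.4% and 1.9% (70 volumes, 100 EEG features, 5 markers) and 1.2%, 4.3% and 9.7% (noisier brain measures). The answer follows the assumed structure as much as the biology.

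**4. Direct look at the path.** In the simulation of step 2, the correlation of mean inflammation with the mean of the 8 affected regions was 0.00 with no effect, −0.43 and −0.68 under mediation (a = 0.3 and 0.6), and 0.00 for direct action. This separates the three as associations, though it does not remove confounding.

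**The case against.** The best defence has four parts.

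- **Attribution is not blind to a true effect.** A reader might infer that the result is about the same whether inflammation acts through the brain or not at all. The documents do not support that as a general statement. The article itself describes MRI and EEG as noisy, and with noisy brain measures the inflammation share rises with mediation. Under joint PCA in the second step it rose from 1.4% to 8.9% and 16.7%. This stands, and it limits the point.
- **PCA need not hide the markers.** A reader might infer that only components mixing all modalities can be scored. The article does not say the PCA is joint, and a linear reduction lets attributions be carried back to named markers and regions. This also stands.
- **No rule is stated for reading ranks.** The article sets no top-k cut-off and does not say that a low score means inflammation is unimportant. The AUC target is unaffected by SHAP or LIME. Correct; those misreadings are risks, not planned rules.
- **Inflammation is examined elsewhere.** The secondary correlations and group comparisons do look at inflammation against brain measures. They are the sounder basis, but mediation is not named for inflammation there, and the mechanism statement is not made conditional on those results.

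None of this reaches the core: even where the share responds, it responds alike to mediated, confounded and suitably sized direct action.

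**Conclusion.** The concern holds in a limited form. The planned attribution cannot establish how inflammation affects brain development, because it does not identify the path. That conclusion follows from the model's structure, and the shared-cause equality is exact.

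The weaker distinction, mediated action against none, has no fixed size. The inflammation share is 0% in both cases with a fully captured mediator. At reliability 0.7 it is 0% against 10.6% (a = 0.3) in the worked case. In the many-feature simulation it is 4.9% against 5.0% within modality and 1.4% against 8.9% under joint PCA. Noise, effect size and the form of PCA decide it.

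The figures rest on linear surrogates and assumed inputs. No Transformer was fitted and LIME was not simulated. The predictive aim and its AUC target are untouched; what must change is the conclusion drawn from the model under a primary outcome.

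**What to change.** In Construction of infant brain development models, limit SHAP and LIME to describing which inputs the predictor uses, and withdraw the statement that they explain how inflammation affects brain development.

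Base that conclusion on an extension of the planned CRP/IL-6 analyses: the total effect of inflammation on the brain measures and on developmental outcomes, from models that adjust for confounders and do not condition on the brain measures. If a statement about the path through the brain is wanted, plan a mediation analysis for inflammation with its assumptions stated.

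Report the change in held-out AUC with and without the inflammation block, with a confidence interval from resampling children, and present it only as added predictive value.

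Cost: revised wording and a few extra model fits on data already planned, with no new collection. The price is a more modest mechanistic claim.

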##### Gene-environment interaction

In the data analysis of gene–environment interactions, this study will be base on whole exome sequencing data. First, variant detection and quality control will be performed using the Genome Analysis Toolkit (GATK). ANNOVAR will be utilized for functional annotation of the variants, and high-quality loci will be screened through the Hardy-Weinberg Equilibrium (HWE) test. We will focus on the variants of candidate genes related to brain development and loss-of-function mutations. Subsequently, the Sequence Kernel Association Test with Optimal weighting (SKAT-O) will be employed to analyze the association between gene sets and brain development phenotypes. Meanwhile, a generalized linear model will be constructed, incorporating pregnancy inflammation indicators (such as CRP and IL-6 levels), environmental exposure variables, and their interaction terms with gene variants to test the gene–environment interaction effects. By referring to the literature in fields such as neural synapse development and inflammatory signaling pathways, genes with significant effects in the interaction will be screened out. For the screened genes, methods such as metabolomics and proteomics will be further used to verify their regulatory mechanisms in brain development, analyze the impact of genes on the early-life brain structure and function of infants, and ultimately reveal the molecular pathways through which the interaction of genes, pregnancy inflammation, and environmental exposure affects early brain development. It is expected to identify at least 10 key genes with significant effects and clarify their potential biological mechanisms.

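### The gene-set rare-variant test covers only the main association; the interaction relies on variant-level GLM terms, which have very little power for rare and loss-of-function variants

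*Protocol article*

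**What the plan says.** The protocol article's Data analysis section on gene–environment interaction works from whole-exome data and makes three choices in sequence.

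- Genetic scope: "We will focus on the variants of candidate genes related to brain development and loss-of-function mutations". Candidate-gene variants and loss-of-function mutations are both in scope, and no allele-frequency limit is given.
- Main association: SKAT-O "will be employed to analyze the association between gene sets and brain development phenotypes".
- Interaction: a GLM with inflammation indicators (CRP and IL-6 levels are the examples) and "environmental exposure variables, and their interaction terms with gene variants to test the gene–environment interaction effects".

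Genes with a significant interaction then go forward to metabolomic and proteomic work, and the section closes with a target: "It is expected to identify at least 10 key genes with significant effects". The section of the same name under Primary outcome also sets at least 10 genes as the target and ties it explicitly to interaction effects.

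The Follow-up plan gives the planned analysable cohort as "totaling 3,216 participants". Sample size assumes a 1:1 ratio of inflammatory to normal mothers. Preliminary results reports 360 pairs enrolled, 187 of them with maternal inflammation.

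**The concern.** SKAT-O pools variants within a set because rare variants are too sparse to test singly. The plan uses this kind of pooling for the main association but names no counterpart for the interaction, where sparsity bites harder because carriers are also spread over the exposure. The primary outcome is counted in genes, whereas the stated model term is the variant.

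If rare and loss-of-function variants enter the interaction model as individual terms, many terms will rest on a handful of carriers or none. Real gene-level interactions would then be missed. Whatever passes the screen decides where the laboratory follow-up goes.

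**Working it through.** **The plan's own figures.** The plan gives no power, carrier count or detectable effect for this analysis, so there is none to reproduce. The cohort total it rests on does reproduce: 3 × 536 + 6 × 268 = 3,216, or 1,608 per group at 1:1.

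**Inputs.** From the article: 3,216 planned children, the 1:1 ratio, and 360 enrolled (187 with and 173 without maternal inflammation). Assumed, because the article gives no figure: carrier frequency f (range shown), two exposure groups as a simplification, and thresholds of 0.05, 0.0005 (0.05/100 tests) and 0.0001 (0.05/500 tests).

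**Formulas.** Carriers per group c = 1,608 × f. With the interaction as a difference of differences in SD units, SE = √(2/c + 2/(1,608 − c)). The smallest interaction detectable with 80% power is (z for two-sided α + 0.842) × SE.

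| Carrier frequency f | Carriers per group | Detectable at 0.05 | Detectable at 0.0001 |
|---|---|---|---|
| 0.02% | 0.3 | not usable | not usable |
| 0.1% | 1.6 | 3.1 SD | 5.3 SD |
| 0.2% | 3.2 | 2.2 SD | 3.7 SD |
| 0.5% | 8.0 | 1.4 SD | 2.4 SD |
| 1% | 16 | 1.0 SD | 1.7 SD |
| 2% | 32 | 0.7 SD | 1.2 SD |
| 5% | 80 | 0.45 SD | 0.8 SD |

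Worked line at f = 0.2% (an allele frequency of about 0.1%): SE = √(2/3.22 + 2/1,605) = 0.79. Then (1.960 + 0.842) × 0.79 = 2.2 SD, and (3.891 + 0.842) × 0.79 = 3.7 SD. Power for a 1 SD interaction at 0.05 is about 24%.

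**Gain from pooling.** If the qualifying variants of a gene together reach 1–2% carriers (assumed), the relevant rows are the 1% and 2% ones: 0.7–1.0 SD at 0.05 and 1.2–1.7 SD at 0.0001.

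**The 360 enrolled.** At f = 0.2% the expected carriers are 187 × 0.002 = 0.37 and 173 × 0.002 = 0.35. The Poisson chance that at least one carrier group is empty is 1 − (1 − e^−0.37)(1 − e^−0.35) = 91%. It is 65% at f = 0.5% and 30% at f = 1%. So most terms at 0.5% or below could not be estimated in these children.

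**Type I error.** The interaction t-test was simulated with no true effect, 1,608 children per group and 3 + 3 carriers (40,000 runs).

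| Outcome distribution | Error at nominal 5% | Error at nominal 0.05% |
|---|---|---|
| Normal | 5.2% | 0.04% |
| Gamma, skewness 1 | 5.3% | 0.12% |
| Exponential | 5.8% | 0.31% |
| Log-normal | 5.4% | 1.0% |

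At 5% the error is close to nominal. At 0.05% (α = 0.0005) it is about 2 to 20 times nominal for the skewed outcomes. The Z-scores planned for behaviour data under Cohort and data objectives are a linear rescaling and leave skew unchanged.

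**The case against.** The strongest reply is that the article is condensed. It speaks of interaction terms with gene variants but does not say they are tested one at a time, and a carrier or burden indicator can be a term in a GLM. The next step screens genes, so the reporting unit may already be the gene. Genetic and exposome testing also lists whole-gene and multi-gene methods. Variant coding and carrier minimums commonly sit in the full plan.

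Part of this stands. One-at-a-time testing is the natural reading, not a stated rule. But the whole-gene methods are listed for whole-genome work on molecular mechanisms and are not tied to the interaction. The article does name a method for each question, and the aggregate one goes only to the main association. The point therefore concerns a stated choice, not an omitted detail.

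Four stronger readings are tempting but unsupported:

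- *That about three carriers per exposure group is a fact of the plan.* It follows only from an assumed carrier frequency of 0.2%; the range is 0.3 to 16 for 0.02–1%.
- *That the work is confined to loss-of-function variants.* Commoner candidate-gene variants are also in scope and much less affected (0.45 SD detectable at 5% carriers and α = 0.05).
- *That skewed scores would fill the 10-gene list with chance findings.* The article states neither skew nor a threshold. Even with 500 tests at 0.0001 and assumed error rates of 0.0013–0.0047, the expected false hits are 500 × 0.0013 = 0.7 to 500 × 0.0047 = 2.4 per outcome and exposure, short of 10.
- *That pooling solves the power problem.* At 0.0001 it still needs 1.2–1.7 SD.

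It is also fair that CRP and IL-6 enter as levels, so two groups is a simplification. It does not dissolve the sparsity: with six carriers, a continuous exposure and skewed outcomes, simulated error at nominal 0.0001 was still roughly 8–35 times too high, and it stayed nominal for normal outcomes.

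**Conclusion.** The concern holds as a mismatch between method and question. The plan applies gene-set testing to the main association but specifies the interaction at variant level, although loss-of-function mutations are one focus and the outcome is counted in genes. The main consequence is lost power for rare variants: about 2.2 SD detectable at 0.05 and 3.7 SD at 0.0001 if 0.2% of children carry the variant, against 0.7–1.0 SD and 1.2–1.7 SD if pooling brings a gene to 1–2% carriers. These sizes rest on assumed carrier frequencies, the full 3,216 children, a 1:1 split and a two-group exposure.

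Inflated type I error is a secondary, conditional risk. It needs both skewed outcomes and a multiplicity-corrected threshold. A reader might infer that the planned gene list would consist of artefacts; the article and the arithmetic do not support that.

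**What to change.** State the unit of the interaction test by variant class.

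- For rare and loss-of-function variants, test at gene level: a carrier or burden score multiplied by inflammation level, together with a SKAT-type kernel interaction test.
- Set a minimum number of carriers, with adequate spread over the exposure, below which a gene is not tested for interaction.
- For sparse genes, use rank-normalised outcomes or resampling p-values.
- Keep single-variant interaction terms for common variants, with the frequency limit stated.

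The cost is a change of analysis wording using existing software; no new data are needed. The downside is that a single strong variant in a gene with mixed effects is somewhat diluted in the burden test, which the kernel test partly recovers.

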#### Brain imaging data

At each follow-up visit, the data of the brain magnetic resonance examination in the non-sedated state of the subjects were collected, including skull structure MRI (sMRI), resting-state fMRI, dMRI sequence and multi-parametric MRI (MTP) scans for a total of 40 min. All MRI data were acquired on a 3T scanner (uMR 890, United Imaging) with a 64-channel head coil. The scanning protocol was as follows: Structural MRI: High-resolution T1w/T2w images (0.8 mm isotropic) using AI-assisted compressed sensing (ACS) (53), achieving 37.8% time reduction compared to BCP protocols (5). Resting-state fMRI: Single-shot EPI (TR = 800 ms, 1.8 mm isotropic) with multiband factor = 8 and field-map-based distortion correction. Diffusion MRI: 72 directions with 3 shells (*b* = 500/1,000/3,000) and dual phase-encoding, utilizing incremental acquisition for sampling uniformity (54). Multi-parametric MRI (MTP): Gradient-echo sequences generating PDw/T1w/T2w images and quantitative maps (PD/T1/T2/QSM) through dual-TR/dual-flip-angle design. Automated slice positioning (Easy Scan) was used to standardize scan planning. For sleeping subjects, supplemental scans (fMRI with reversed phase-encoding; dMRI at *b* = 1,500/2,000/2,500) were added to mitigate geometric distortions. The detailed MRI acquisition protocol is summarized in Table 3.

**Table 3 T3:** The parameter list of the multi-MRI protocol (12, 54, 55).

**Sequence**		**Matrix**	**FoV (mm)**	**Resolution (mm)**	**TE (msec)**	**TR (msec)**	**Slices/orientation**	**Time (min:sec)**	**Acceleration strategy**
Localizer		115 × 144	300 × 300	2.6 × 2.08 × 4	1	2.7	1/Sag	00:10	-
T1-weighted		320 × 300	256 × 240	0.8 × 0.8 × 0.8	2.9	7.4	208/Sag	03:44	ACS, × 3.3
T2-weighted		320 × 300	256 × 256	0.8 × 0.8 × 0.8	452	3,000	208/Sag	04:09	ACS, × 3.8
Field Map		116 × 116	209 × 209	1.8 × 1.8 × 1.8	2.46	501.2	72/Axial	00:58	-
BOLD Rest Ref PA		116 × 116	209 × 209	1.8 × 1.8 × 1.8	35	800	72/Axial	00:25	Multi-band = 1
BOLD Rest PA		116 × 116	209 × 209	1.8 × 1.8 × 1.8	35	800	72/Axial	06:25	Multi-band = 8
DWI b0 AP		140 × 140	210 × 210	1.5 × 1.5 × 1.5	77.5	3,000	92/Axial	00:40	Multi-band = 4
DWI	PA, *b* = 500, 1,000, 3,000	140 × 140	210 × 210	1.5 × 1.5 × 1.5	77.5	3,014	92/Axial	04:29	Multi-band = 4, 3 shells, 72 directions
	AP, *b* = 1,500, 2,000, 2,500	140 × 140	210 × 210	1.5 × 1.5 × 1.5	77.5	3,014	92/Axial	04:29	
MTP		192 × 192	230 × 190	0.8 × 0.8 × 1.6	20.76	36.8	70/Axial	7:10	ACS, × 4

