##### The impact of family environment and parenting patterns on brain development

Regarding the secondary research results, we will conduct a comprehensive analysis from two aspects: the exposure of adverse factors in mothers during pregnancy and the family environment and parenting patterns after birth. For maternal exposure to adverse factors during pregnancy, on the one hand, regarding the correlation between inflammatory indicators and brain development, we will conduct correlation analysis between brain indicators such as MRI-derived brain volume, cortical thickness, and EEG power spectral density, and the levels of inflammatory cytokines such as C-reactive protein (CRP) and Interleukin-6 (IL-6). Group children according to the inflammatory levels and compare their brain imaging, electrophysiological data, and scores of relevant abilities of children. On the other hand, for other adverse conditions during pregnancy, conduct regression analysis to explore the potential links with the future development of children. In the analysis of family factors after birth, first conduct correlation and regression analysis between the scores of the quantified family parenting scale and brain indicators such as MRI-derived brain volume, cortical thickness, and EEG power spectral density. At the same time, explore the pathways through which parenting patterns affect children's intellectual development through mediation analysis. In addition, associate family environment variables with children's emotional regulation indicators, and compare the differences in children's cognitive development under different parenting styles.

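### The gene-environment and inflammation analyses name methods for independent observations, while MRI and EEG are repeated 3–4 times per child and the unit of analysis is not stated

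*Protocol article*

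**What the plan says.** The Gene-environment interaction part of Data analysis names two methods. For gene sets, "the Sequence Kernel Association Test with Optimal weighting (SKAT-O) will be employed to analyze the association between gene sets and brain development phenotypes". For interactions, "a generalized linear model will be constructed, incorporating pregnancy inflammation indicators", together with environmental exposures and their products with gene variants. No child-level term, clustering, robust variance or per-child summary is mentioned, and the phenotype is not tied to a visit or an age.

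The section on family environment and parenting (secondary outcomes) is similar: "we will conduct correlation analysis between brain indicators such as MRI-derived brain volume, cortical thickness, and EEG power spectral density" on one side and inflammatory markers on the other, followed by comparisons of children grouped by inflammatory level.

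The outcome data are repeated. The Follow-up plan states: "Each of the first three sub-cohorts enrolled 536 participants, while sub-cohorts 4–9 each enrolled 268 participants, totaling 3,216 participants". It adds: "Each participant was followed up 3–4 times, yielding data from 11,256 participant—visits". Brain imaging data opens with "At each follow-up visit, the data of the brain magnetic resonance examination", and EEG examination sets the same frequency for EEG. Blood for sequencing and exposome work is drawn once, at enrolment. The gene-environment target, at least 10 genes with significant interaction, stands under Primary outcome.

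**The concern.** Genotype and maternal inflammation during pregnancy do not change between a child's visits. A second or third scan of the same child therefore brings less new information about these predictors than a scan of another child. If every visit enters an ordinary regression as a separate row, the standard error is too small by the square root of the design effect, and tests reject too often. The outcome at stake is defined by significance. A stricter threshold for the number of genes does not repair a wrong standard error.

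The other route, one row per child, is sound for these methods but needs a rule, because the sub-cohorts are seen at different ages. Without a rule, the analyst must choose between correlated rows and a small part of the cohort.

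**Working it through.** **1. Visits, from Table 1.** Sub-cohorts 1–3 have 4 visits each and sub-cohorts 4–9 have 3.
- Children: 3 × 536 + 6 × 268 = 1,608 + 1,608 = 3,216.
- Visits: 1,608 × 4 + 1,608 × 3 = 6,432 + 4,824 = 11,256.
- Mean: 11,256 / 3,216 = 3.5 per child.

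Both of the article's totals are reproduced.

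**2. Can one common age give one row per child?** Sub-cohorts 1–3 end at 9, 10 and 11 months; sub-cohort 9 starts at 24. No age is shared by all.
- The best-covered scheduled months are 6 (sub-cohorts 1 and 5), 9 (1 and 6) and 10 (2 and 4). Each has 536 + 268 = 804 children, and 804 / 3,216 = 25%.
- Age bands from Table 2 reach more children but bring repeats back. The 7–12 month band covers sub-cohorts 1–7: 3 × 536 + 4 × 268 = 2,680 children, with sub-cohorts 2 and 3 seen twice (months 7 and 10; 8 and 11).
- The 25–36 month band, the only one with the WPPSI-IV, covers sub-cohorts 8 and 9: 536 children, with sub-cohort 9 seen twice.

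**3. Error rate if visits are pooled.** The article gives neither a within-child correlation ρ nor a significance level for the gene tests. Assumed here: ρ of 0.3, 0.5 and 0.8, equal between any two visits of a child; two-sided 5%; predictors constant within a child.
- Σm² / Σm = (1,608 × 16 + 1,608 × 9) / 11,256 = 40,200 / 11,256 = 3.571.
- Design effect DE = 1 + (3.571 − 1) × ρ = 1 + 2.571ρ.
- Actual error = 2 × [1 − Φ(1.96 / √DE)].

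| ρ | DE | Equivalent independent rows (11,256 / DE) | Actual error at nominal 5% |
|---|---|---|---|
| 0.3 | 1.77 | 6,354 | 14.1% |
| 0.5 | 2.29 | 4,925 | 19.5% |
| 0.8 | 3.06 | 3,682 | 26.2% |

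Over a wider range, the ratio to nominal is 1.6 at ρ = 0.1 (8.0%) and 5.6 at ρ = 0.9 (28.2%). DE depends on the mix of 3 and 4 visits, not on the number of children.

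**4. Simulation checks.** Both used a linear regression with a gene-by-exposure product, minor-allele frequency 0.2 and no true effect.
- 800 children, half with 4 visits and half with 3, 2,000 replicates: pooled rows rejected in 5.6%, 14.4%, 20.6% and 24.7% at ρ = 0, 0.3, 0.5 and 0.7. One record per child gave 4.5–5.2%.
- The Table 1 visit structure, 1,500 replicates: pooled rows gave 15.3%, 20.4% and 24.4% at ρ = 0.3, 0.5 and 0.8. Child-clustered standard errors gave 4.5–5.9%.

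SKAT-O itself was not simulated.

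**The case against.** The strongest reply is that the article never says visits are stacked. The phenotype has no unit attached, and a single-age value or a per-child trajectory feature fits the wording. Some text leans towards the child as the unit: the sample size counts mothers in two independent groups, the secondary analysis groups children by inflammatory level, and the genetics section speaks of developmental trajectories. The ordinary forms of the two methods are valid for one record per child. An article may also leave covariance details to an analysis plan that is not shown.

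Most of this stands, and it rules out two stronger readings. A reader might infer that false positives are inflated about fourfold. That needs pooling, ρ near 0.5 and a 5% level together, and the article states none of them; with one value per child the factor is 1. A reader might also infer that the count of significant genes is inflated by the same factor. The figures are per-test error rates for an interaction regression; the count also depends on how many genes are tested and on true effects.

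What does not stand is that nothing needs changing. The article names a model class, and an analysis plan that followed it literally would have no term for the repeats. The staggered ages mean that one row per child does not arise by default: it takes either a large loss of children or an age-adjusted summary that the article does not name. Where longitudinal modelling is intended, in the brain atlas section, the article says so; here it does not.

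**Conclusion.** The concern holds conditionally. The named methods do not match a design with 3–4 MRI and EEG measurements per child at ages that differ by sub-cohort, and the unit of analysis is open. If visits are pooled as independent rows, the per-test error at nominal 5% is about 14% to 26% for assumed within-child correlations of 0.3 to 0.8. If one value per child is used, the error is nominal, but choosing one scheduled age keeps at most a quarter of the children.

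The percentages rest on the planned visit mix, an exchangeable correlation and predictors fixed within the child; they do not apply to exposures that vary between visits. They show what is at risk under one reading and do not establish that the study's results are inflated. The change is worth making because it is valid under either reading, but the documents do not show an error that invalidates the analysis.

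**What to change.** In the Gene-environment interaction section, state the unit of analysis. Replace the generalized linear model with a mixed model that has a child random intercept and age at visit as a covariate, or with a GEE clustered on child. Run SKAT-O on one age-adjusted value per child, for example the child's mean or slope derived from that mixed model, or use a mixed-model version of the test. In the section on family environment and parenting, apply the same child-level rule to the MRI and EEG correlations, regressions and group comparisons.

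The cost is a few sentences and standard software; no new data are needed, and all visits can be used. The downside is wider intervals, and possibly fewer significant genes, than naive pooling would give.
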